## Abstract

**Background:**

It is crucial to provide care based on individual needs. Swedish health care is obliged to give care on equal conditions for the entire population. The person with the greatest need should be given the most care, and the health care system should strive to be cost-efficient. Medical and technical advances have been significant during the last decades and the recent Covid-19 pandemic has caused a shift in health care, from in-person visits to virtual visits. The majority of pregnant women with a low risk assessment have an uncomplicated antenatal course without adverse events. These women probably receive excessive and unnecessary antenatal care. This study will investigate if an antenatal care program for healthy pregnant women with a low risk for adverse outcomes could be safely monitored with fewer in-person visits to a midwife, and with some of them replaced by virtual visits.

**Methods:**

This is a non-inferiority trial where a stepped wedge cluster randomized controlled design will be used. Data collection includes register data and questionnaires that concern antenatal, obstetric and neonatal outcomes, patient- and caregiver-reported experiences, healthcare-economy, and implementation aspects. The modified antenatal care (MAC) study is performed in parts of the southeast of Sweden, which has approximately 8200 childbirths annually. At the start of the study, all antenatal care centers included in the study will use the same standard antenatal care (SAC) program. In the MAC program the in-person visits to a midwife will be reduced to four instead of eight, with two additional virtual meetings compared with the SAC program.

**Discussion:**

This presented study protocol is informed by research knowledge. The protocol is expected to provide a good structure for future studies on changed antenatal care programs that introduce virtual visits for healthy pregnant women with a low risk for adverse outcomes, without risking quality, safety, and increased costs.

**Trial registration:**

The study is registered the 21th of April 2021 in the ISRCTN registry with trial ID: ISRCTN14422582, retrospectively registered.

**Supplementary Information:**

The online version contains supplementary material available at 10.1186/s12884-022-04406-7.

## Background

Historically, antenatal care programs were mainly developed to detect preeclampsia and gestational diabetes mellitus. Medical and technical advances in the last decades and new tests to detect complications e.g. the oral glucose tolerance test and screening for the risk of preeclampsia have been included in the antenatal care. There is a lack of evidence on the effectiveness, frequency and timing of the scheduled antenatal care visits. Studies regarding antenatal care programs has looked at different models and concluded that a reduction in the number of antenatal care visits during pregnancy is safe regarding neonatal and obstetric outcomes [1]. Also, no differences have been shown in adverse events when considering women having antenatal visits to an obstetrician, compared to midwives or general practitioners [2]. The clinical content of the antenatal care program has been subject to several evaluations and is still controversial. Most guidelines recommend routine assessment with fundal height, maternal weight, blood pressure measurements, fetal heart auscultation, urine testing for protein and questions about fetal movements. The evidence supporting these practices is variable and in most cases, no association between the assessment and improved maternal or fetal outcomes has been proven [3–8]. In addition, antenatal care has three main psychological functions: to provide information, social support and reassurance for reducing antenatal and postnatal morbidity. Studies have shown that the quality of the visit is crucial for the patient’s satisfaction rather than the number of visits to the midwife [9–11].

The recent Covid-19 pandemic has caused a shift from in-person visits to virtual visits. Peahl et al. conducted a study in 2020 with a redesign of the antenatal care for pregnant women with a low risk, consisting of four in-person visits, one obstetric ultrasound and four virtual visits [12]. E-health has become a promising option for providing healthcare, and early trials using virtual care and remote monitoring have shown high patient satisfaction [13].

The current standard antenatal care (SAC) program was developed by the Swedish national reference group for maternal health care during the early 1990s and has undergone some minor revisions regarding frequency and timing of the scheduled midwife visits during the last decades. At the same time, the medical content has expanded, now including for example screening for anemia, thyroid disease, evaluation for thromboembolic risk and anti-Rhesus immunization during pregnancy.

The SAC program in Sweden is free of charge with a high attendance rate of almost 100%. There is no longer a routine visit to an obstetrician for all pregnant women, but instead the midwife carries out a risk assessment based on national guidelines in early pregnancy. The risk assessment determines if the SAC program is sufficient or if extra visits are needed, i.e., for an ultrasound for fetal growth or an appointment with an obstetrician.

According to the Swedish Health Care Act, publicly funded care is obliged to follow ethical principles for prioritization and resource allocation, namely the human dignity principle, the need-solidarity principles and the cost-effectiveness principle. That means that all people must be treated with respect for their dignity and considered as having equal value, those with the greatest need for health care should be given priority, and health care activities should be organized so that cost-effectiveness is promoted [14]. The majority of pregnant women with a low risk assessment in early pregnancy have an uncomplicated antenatal course without adverse events during pregnancy and childbirth [15]. These women probably receive excessive and unnecessary antenatal care in Sweden today.

The proportion of women with a high risk for complications during pregnancy and childbirth is increasing due to e.g. obesity, advanced age or intercurrent diseases [16, 17]. It is therefore important to individualize the antenatal care visits to a greater extent and make a resource-shift toward those who need more care. That is to ensure that the resources are appropriately and efficiently distributed to the care of those with the greatest need, which is of particular importance in a publicly funded health care system.

Our hypothesis is that the modified antenatal care (MAC) program does not differ in regard to antenatal, obstetric and neonatal outcomes compared to the SAC program. We also hypothesize that the cost of the MAC program is lower than the cost of the SAC program. We also assume that selected implementation strategies will support a high level of adherence and sustainability for the MAC program.

This study protocol will describe the guideline development of a MAC program. The study design and methods aimed to investigate if a reduction in-person visits to a midwife with some of those visits replaced with virtual visits is safe for healthy pregnant women with a low risk for adverse outcomes. The planned study will evaluate a MAC program in comparison to the SAC program for healthy pregnant women with a low risk for adverse outcomes, considering the following aspects: maternal- and neonatal outcomes, patient- and caregiver-reported experiences, healthcare economy, and will also evaluate the MAC program implementation.

## Methods

### Study design

This is a stepped wedge cluster randomized controlled trial comparing two different programs: the standard antenatal care (SAC) program and the modified antenatal care (MAC) program in five antenatal care centers (ACC) where each participating ACC constitutes one cluster (A-E). All visits to both the SAC and MAC take place in an ACC in the South East region of Sweden. At the start of the study, all ACCs will use the same and current SAC program. The healthy pregnant women with a low risk for adverse outcomes, who are attending the current SAC program will constitute the control group. After the start of the MAC program, the corresponding women will constitute the index group.

### Procedures

#### Guideline development

To scrutinize all aspects of antenatal care, we first assembled a research team consisting of senior consultants in maternity and obstetric care, midwives, a health economist, experts in implementation strategies, and in the later stages also statistics experts, hospital administration staff, health communicators, IT consultants and executives. We used systematic literature reviews and PubMed searches to investigate existing evidence in the fields of antenatal care and e-health. After having drawn up the recommended checks during pregnancy, they were divided into two categories: the ones who we assumed would need in-person visits i.e., ultrasounds, laboratory tests and physical examination, and the others that we assumed could be offered remotely through virtual meetings, mainly concerning information and reassurance. These controls were thereafter grouped, based on their recommended timing during pregnancy. With the introduction of the MAC program the in-person visits to a midwife will be reduced to four instead of eight, including the visit with the risk assessment, with two additional virtual meetings. Two obstetric ultrasounds are conducted in both the SAC and MAC, see Table 1. The first meeting in both the SAC and the MAC program is an in-person visit to establish a bond of trust between the pregnant woman and the midwife. That has been shown to be preferred by both patients and caregivers when using blended care, i.e., mixing in-person visits and virtual visits [18, 19]. During this visit a thorough risk assessment is carried out and the midwife determines if the pregnant women has a low or high risk for complications during pregnancy, see Supplement 1. In early pregnancy, before the risk assessment visit, information about recommended life-style changes in pregnancy is given to the pregnant women.

**Table 1 Tab1:** Main medical content in the standard antenatal care program (SAC) and the modified antenatal care program (MAC)

	**SAC**		**MAC**		
Gestational week	In-person visit	Medical content e.g	In-person visit	Virtual visit	Medical content e.g
6 to 10		Lifestyle recommendations			Lifestyle recommendations
11 to 15	# 1	Risk assessment Gynecological examination Blood pressure Prenatal labs Urine testing for protein	# 1		Risk assessment Gynecological examination Blood pressure Prenatal labs Urine testing for protein
11 to 13 + 6	yes	Obstetrical ultrasound with preeclampsia risk assessment	yes		Obstetrical ultrasound with preeclampsia risk assessment
18 + 0 to 20 + 0	yes	Obstetrical ultrasound	yes		Obstetrical ultrasound
25	# 2	Blood pressure Fetal heart rate with Doppler Symphysis fundus height Plasma-glucose		# 1	Up-dating history
29	# 3	Blood pressure Fetal heart rate with Doppler Symphysis fundus height Plasma-glucose Blood tests Urine testing for protein	# 2		Blood pressure Fetal heart rate with Doppler Symphysis fundus height Plasma-glucose Blood tests Urine testing for protein
32	# 4	Blood pressure Fetal heart rate with Doppler Symphysis fundus height			
35	# 5	Blood pressure Fetal heart rate with Doppler Symphysis fundus height Fetal presentation	# 3		Blood pressure Fetal heart rate with Doppler Symphysis fundus height Fetal presentation
37	# 6	Blood pressure Fetal heart rate with Doppler Symphysis fundus height Fetal presentation			
38			# 4		Blood pressure Fetal heart rate with Doppler Symphysis fundus height Fetal presentation
39	# 7	Blood pressure Fetal heart rate with Doppler Symphysis fundus height Fetal presentation			
41	# 8	Blood pressure Fetal heart rate with Doppler Symphysis fundus height Fetal presentation Membrane sweep		# 2	Up-dating history

The information given during pregnancy to the pregnant women is listed in Table 2. In early pregnancy and during the virtual meeting in gestational week 25 most of the information is provided.

**Table 2 Tab2:** Information given during pregnancy in the standard antenatal care program (SAC) and the modified antenatal care program (MAC)

**Antenatal care program**	SAC/MAC	SAC/MAC	SAC/MAC^a^	SAC/MAC	SAC	SAC	MAC	SAC/MAC
Gestational week	6 to 10	11 to 15	25	29	32	35	35	37/38
Type of information related to pregnancy								
Diet	X		X					
Tobacco	X		X		X		X	
Alcohol	X				X		X	
Medication/Drugs/Violence	X							
Exercise/Sex	X							
Prenatal testing	X							
Social insurance system		X						
Fetal movement			X					
Parent support			X					
Breastfeeding			X					
Family law				X				
Delivery and maternity ward				X				
Contraception								X

*SAC* standard antenatal care program, *MAC* Modified antenatal care program

**Table 3 Tab3:** Variables included in the composite outcomes and other variables for evaluation of the MAC program

Antenatal care outcomes	Obstetric outcomes	Neonatal outcomes
Question about experience of violence and alcohol habits Recommended weight gain for women with body mass index (BMI) 19.0–29.9 Fear of childbirth-counselling	Premature birth < gestational week 34 + 0 Pregnancy-induced hypertension Preeclampsia Eclampsia	Small for gestational age Large for gestational age Apgar > 7 at 5 min Admission to neonatal intensive care unit
Tobacco use Breastfeeding initiation Breastfeeding 4 weeks postpartum Treatment for mental illness Self-judged health	Gestational diabetes mellitus Anemia Urinary tract infection Pregnancy complications e.g. intrahepatic cholestasis, premature contractions	Intrauterine fetal death Other neonatal complications e.g. jaundice, hypoglycemia
Newborn small for gestational age that has been identified	Undiagnosed fetal breech presentation Induction of labor Vaginal birth after cesarean Instrumental delivery Cesarean section Maternal death

**Table 4 Tab4:** Direct and Indirect costs to be evaluated in the MAC study

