### Outcomes

#### Health

This is a non-inferiority trial with the aim of determining if the MAC program differs in quality and safety compared with the SAC program as regards antenatal, obstetric and neonatal outcomes, including satisfaction of the patient and caregiver. The cost-effectiveness and the implementation of the program will also be assessed. Many outcomes measured in this study are rare, since the MAC program only involves a specific low-risk healthy pregnant population. For this reason, some of the outcomes are clustered in the following composites: antenatal care – measuring the national quality measures of the antenatal care program, obstetric- and neonatal outcomes and health care consumption – measuring frequency and setting of visits. The different outcome composites are listed in Tables 3 and 4.

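### Table 3 lists Apgar > 7 at 5 min, the healthy state, among otherwise adverse neonatal outcomes: an apparent sign error that would reverse this item in the neonatal composite

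*Protocol article*

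**What the plan says.** Table 3 of the protocol article has three columns: antenatal care, obstetric and neonatal outcomes. The neonatal column starts with "Small for gestational age Large for gestational age Apgar > 7 at 5 min Admission to neonatal intensive care unit" and continues with "Intrauterine fetal death Other neonatal complications e.g. jaundice, hypoglycemia". The last block of the obstetric column reads "Undiagnosed fetal breech presentation Induction of labor Vaginal birth after cesarean Instrumental delivery Cesarean section Maternal death".

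The caption describes the content as "Variables included in the composite outcomes and other variables for evaluation of the MAC program". The Health section under Outcomes gives the reason for composites, "Many outcomes measured in this study are rare, since the MAC program only involves a specific low-risk healthy pregnant population". It then says that "some of the outcomes are clustered in the following composites", and closes with "The different outcome composites are listed in Tables 3 and 4". It also describes the trial as a non-inferiority comparison of quality and safety.

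The section on sample size and power names the obstetric composite as the primary outcome. The text shown does not mark which variables belong to a composite, the direction of each item, or how a composite is scored.

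**The concern.** Small and large for gestational age, admission to intensive care, fetal death, and complications such as jaundice are all things one hopes not to see. An Apgar score above 7 at five minutes is what one hopes to see. As printed, a healthy baby satisfies an item in a list of neonatal harms.

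This matters because the trial asks whether fewer in-person visits are safe. A non-inferiority conclusion depends on which direction counts as worse. If the item were coded as printed, the neonatal composite would be close to saturated, other harms would hardly move it, and a rise in low Apgar scores would push it in favour of the modified program.

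A second item needs a check for the same reason. Vaginal birth after cesarean is usually a favourable result, and it is listed beside cesarean section in the column from which the primary composite is drawn.

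**Working it through.** **The plan's own figure.** The only related figure is the 4% detectable difference for the obstetric composite. It cannot be reproduced, because neither the composite rate nor the intracluster correlation is given. With 46 women per cluster-month, ten steps with one cluster per step, 5% two-sided significance and 80% power, a standard stepped-wedge calculation gives 2.4 to 6.8 points over assumed rates of 5-50% and correlations of 0.001-0.05. The figure of 4% lies inside that range. Nothing below depends on it.

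**Is the direction really wrong?**
- All other neonatal items in Table 3 are adverse.
- The stated reason for composites is rarity. Apgar above 7 in healthy low-risk pregnancies is not rare.
- A lost less-than sign is an unlikely explanation: the same table row prints one correctly in the premature-birth item.

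**Inputs for the size.** None of these is in the article; all are assumptions.
- *a*, the share of newborns with Apgar above 7: 95-99%.
- *q*, the rate of any other neonatal item: 5-30%.
- Scoring: any listed event.

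**Saturation.** The any-event rate lies between max(*a*, *q*) and min(1, *a* + *q*). It is therefore at least 95-99% as printed. Under independence it is 1 − (1 − *a*)(1 − *q*):
- *a* = 0.95, *q* = 0.05: 1 − 0.05 × 0.95 = 95.25%.
- *a* = 0.99, *q* = 0.30: 1 − 0.01 × 0.70 = 99.3%.

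With the item turned to its complement, the rate is 1 − *a*(1 − *q*) under independence:
- *a* = 0.99, *q* = 0.05: 1 − 0.99 × 0.95 = 5.95%.
- *a* = 0.95, *q* = 0.30: 1 − 0.95 × 0.70 = 33.5%.

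**Loss of sensitivity to other harms.** Hold *a* at 0.97 and let *q* double from 5% to 10%:
- As printed: 97.15% to 97.30%, a rise of 0.15 points.
- Adverse coding: 7.85% to 12.70%, a rise of 4.85 points.

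**Reversal.** Hold *q* at 15% and let low Apgar double from 3% to 6%:
- As printed: 1 − 0.03 × 0.85 = 97.45% falls to 1 − 0.06 × 0.85 = 94.90%.
- Adverse coding: 1 − 0.97 × 0.85 = 17.55% rises to 1 − 0.94 × 0.85 = 20.10%.

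The two changes are equal and opposite, 0.03 × 0.85 = 2.55 points. For a doubling from 1% to 2% they are 0.01 × 0.85 = 0.85 points (99.15% to 98.30%, against 15.85% to 16.70%).

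**Dependence on independence.** Without that assumption, the printed composite equals 1 − P(low Apgar and none of the other items). If babies with low scores usually have another item as well, such as admission, the composite is still closer to 100% and the reversal shrinks towards no signal. Coding the item as printed does not make an increase in low Apgar count as harm in either case.

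**Vaginal birth after cesarean.** A woman with an earlier cesarean gives birth either vaginally or by cesarean. If both items were events in one any-event composite, her probability of an event would be 1 however she delivers.

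**The case against.** The strongest reply is that the table does not establish membership. Its caption also covers other variables, and the Health section clusters only some of the outcomes. Marks that separated components from other variables could have been lost when the table was read from the PDF. The scoring rule is not stated either and may properly be left to the full protocol or analysis plan. Finally, the Apgar item looks like a visible misprint that nobody would code literally, and it lies outside the primary outcome.

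Most of this stands, and it limits the point. The 95-99% figure needs membership, any-event scoring, literal coding and an assumed Apgar share together. It does not remove the point: the same section refers the reader to these tables for the composites, so the inequality is a statement in the outcome definition. Even as a stand-alone variable, or in a count score, the item would have the wrong sign in a list of harms.

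Three stronger readings are tempting and not supported:
- A reader might infer that the primary composite mixes favourable and adverse events, so that its non-inferiority test is uninformative. Nothing shown places vaginal birth after cesarean in that composite. It is in the last block of its column and may be one of the other variables. Eligibility also requires low obstetric risk under a supplement that is not shown, so the number of women with an earlier cesarean is unknown.
- A reader might fault the antenatal column for a list such as "Tobacco use Breastfeeding initiation Breastfeeding 4 weeks postpartum Treatment for mental illness Self-judged health". That column is described as measuring national quality indicators, and such a list may mix directions without error.
- A reader might fault the item on identified small-for-gestational-age newborns for its restricted denominator. A detection measure is naturally restricted in this way.

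**Conclusion.** The Apgar item is stated in the wrong direction for the list in which it stands, most likely through a reversed sign. Taken literally, as a component of an any-event composite, it would put the neonatal composite at 95-99% or more in both groups, if 95-99% of low-risk newborns score above 7. It would also turn an increase in low Apgar scores into an apparent improvement: 2.55 points in the example with low Apgar rising from 3% to 6%, 15% other events and independence. These rates are assumptions and not figures from the article.

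The consequence is confined to the neonatal composite. The primary obstetric composite could be affected only through vaginal birth after cesarean, whose membership is unproven; that is a matter to confirm and not an established error.

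**What to change.** Before data extraction:
1. Restate the Apgar item in Table 3 in the adverse direction, as low Apgar at five minutes, with the cut-off written out. Reversing the sign gives below 7, whereas the complement of the printed item is 7 or below. The two differ for a score of exactly 7, so the sponsor should state which is meant.
2. Confirm that vaginal birth after cesarean is one of the other variables, reported separately, and is not an event in the primary obstetric composite.

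The cost is a wording change to the outcome definitions. No new data item is needed. The sections on data collection and trial status describe extraction as planned, with the first data collection at the end of 2022, so the change can be made before any results are seen.

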### Sample size and power calculation

The sample size was calculated with a stepped wedge sample size add-on program to Stata. The program can only detect minimum difference between two groups for superiority designs; therefore, the program was used to calculate the minimum difference that can be detected with a given sample size. It was estimated that a minimum of 1500 pregnant women a year will be possible for the MAC program. The average number of pregnancies per month in the clusters will be approximately 46 and was inserted in the program in ten steps, excluding the baseline. This study population will be enough for our primary outcome, the obstetric composite. The minimum detectable difference with a p-value of 5% and 80% power will be larger than what is estimated in the main non-inferiority hypothesis, resulting in the effect size of 4%. The analysis will be based on the principle of intention to treat.

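### Hypertension, preeclampsia and gestational diabetes appear in the primary obstetric composite but are checked less often under the modified programme, so for these components missed cases favour non-inferiority

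*Protocol article*

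**What the plan says.** The Abstract (Methods) fixes the framework: "This is a non-inferiority trial where a stepped wedge cluster randomized controlled design will be used". The sample size section names the endpoint: "This study population will be enough for our primary outcome, the obstetric composite". The Outcomes section, under Health, says where its content is found: "The different outcome composites are listed in Tables 3 and 4".

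Table 3 is titled "Variables included in the composite outcomes and other variables for evaluation of the MAC program". Its obstetric column includes "Pregnancy-induced hypertension Preeclampsia Eclampsia" and "Gestational diabetes mellitus Anemia Urinary tract infection Pregnancy complications e.g. intrahepatic cholestasis, premature contractions", along with birth before 34+0, undiagnosed breech, induction, instrumental delivery, caesarean section and maternal death. As the table reads in the available text, nothing marks which entries belong to the composite and which are other variables.

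On the visit schedule, the guideline development section says: "With the introduction of the MAC program the in-person visits to a midwife will be reduced to four instead of eight". In Table 1 the week-25 SAC visit contains "Blood pressure Fetal heart rate with Doppler Symphysis fundus height Plasma-glucose". The MAC contact in that week is virtual and lists only an update of the history. The data collection section takes outcomes from national registers, medical records and local databases.

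**The concern.** Pregnancy-induced hypertension and gestational diabetes enter a record only if someone measures blood pressure or glucose, and preeclampsia is often first suspected from blood pressure. The intervention reduces how often those measurements are scheduled. With the same underlying disease, MAC can show fewer recorded cases than SAC, because part of what the visits do is find the cases.

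In a superiority trial of a treatment meant to lower these rates, this would be a familiar detection bias. In a non-inferiority trial of fewer visits it also hides one of the harms the trial should rule out, since a missed diagnosis scores as a good outcome. The result carries into the economic evaluation as well, where the choice between cost-minimisation and cost-effectiveness analysis depends on whether the programmes' results diverge.

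**Working it through.** **1. Scheduled checks, counted from Table 1**

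| Check | SAC weeks | MAC weeks | SAC vs MAC |
|---|---|---|---|
| Blood pressure | 11–15, 25, 29, 32, 35, 37, 39, 41 | 11–15, 29, 35, 38 | 8 vs 4 |
| Plasma glucose | 25, 29 | 29 | 2 vs 1 |
| Urine protein | 11–15, 29 | 11–15, 29 | 2 vs 2 |
| Prenatal labs and other blood tests | 11–15, 29 | 11–15, 29 | 2 vs 2 |
| Fetal presentation | 35, 37, 39, 41 | 35, 38 | 4 vs 2 |

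The 8 vs 4 count applies to women still pregnant at the week-41 visit. A woman who delivers between the week-39 and week-41 visits has had 7 vs 4 blood pressure checks. One who delivers between weeks 38 and 39 has had 6 vs 4.

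**2. Why the model does not remove it**

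The change in checking starts when a centre switches to MAC and is present only under MAC. In a stepped wedge model it moves with the treatment indicator, so the treatment coefficient absorbs it. Cluster effects and period effects cannot separate it out. Intention to treat does not help either, because the assigned programme is what changes the checking.

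**3. The plan's own figure**

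The sample size section gives a detectable difference of 4% at a 5% p-value and 80% power, with about 46 pregnancies per month and ten steps. It gives no baseline rate and no intracluster correlation, so 4% cannot be reproduced. A generic layout (Hussey–Hughes variance, one cluster per step, 46 per cluster-month, assumed correlations of 0.001 to 0.05) gives 3.3–4.0 points at a 10% baseline rate and 4.4–5.3 at 20%. The order of magnitude is plausible, so 4% is used below only to obtain a standard error.

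**4. Possible size (all inputs assumed)**

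Let p be the proportion of women with one of these diagnoses, m the share of those cases found only at a removed visit, and k the share of those women who count anyway through another component. The shift is

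b = p × m × (1 − k).

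- With k = 0: 6% × 10% = 0.6 points, up to 10% × 20% = 2.0 points.
- With k = 50% at the low end and 30% at the high end: 0.6 × 0.5 = 0.3 points, up to 2.0 × 0.7 = 1.4 points.

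**5. Effect on the error rate (illustration)**

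SE = 4 / (1.96 + 0.84) = 1.43 points. If the true excess under MAC equals the margin, the chance of declaring non-inferiority at one-sided 2.5% is Φ(b/SE − 1.96). It depends on b and SE, not on the margin itself.

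| b (points) | b/SE − 1.96 | False non-inferiority |
|---|---|---|
| 0 | −1.96 | 2.5% |
| 0.3 | −1.75 | 4.0% |
| 0.6 | −1.54 | 6.2% |
| 1.0 | −1.26 | 10.4% |
| 1.4 | −0.98 | 16.4% |
| 2.0 | −0.56 | 28.8% |

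This isolates the loss of detection in these components. It assumes no movement in any other component.

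**The case against.** Several points on the other side carry weight.

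- **Membership.** Table 3 mixes composite components with other variables, so it is not certain that all three diagnoses are in the primary composite. This stands, and it is why the point says they appear to be.
- **Partial loss.** MAC keeps blood pressure at weeks 29, 35 and 38 and glucose at week 29. Extra visits are individualised, and the Discussion describes a prolonged-pregnancy check-up in MAC at the start of week 42. Symptoms and the delivery admission will reveal further cases. A reader might infer from half the visits that half the cases are missed; nothing in the article supports that.
- **Scope.** A reader of the Table 3 row might extend the concern to anemia and urinary tract infection. Table 1 shows no difference in scheduled blood tests other than glucose, nor in urine protein testing, so it gives no basis for that.
- **Net direction.** A reader might infer that the whole composite is biased in favour of MAC. Presentation is checked 4 vs 2 times, so undiagnosed breech may rise in MAC. The later membrane sweep may raise induction, which the authors flag and intend to evaluate. Missed hypertension may progress to events that are counted. The net shift is therefore uncertain. Offsetting errors of unknown size do not make the composite easier to interpret, though.
- **Other safeguards.** Eclampsia, preterm birth, intrauterine death (audited independently), neonatal admission and large for gestational age are all evaluated and could show harm from missed disease. This helps, but most lie outside the primary composite. The planned record review covers missed growth restriction, with no counterpart described for hypertension or glucose.
- **Left to the analysis plan.** Supporting analyses often are. The problem raised here is different: the article itself fixes the endpoint, its listed variables and the unequal schedules.

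**Conclusion.** The concern holds for pregnancy-induced hypertension, preeclampsia and gestational diabetes, provided they are in the primary composite, as Table 3 suggests. For these components the programmes differ in scheduled ascertainment, outcomes come from routine records, and the resulting bias is toward non-inferiority. The planned design and analysis principle do not remove it.

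The size is not derivable from the article. The 0.3 to 2.0 points, and the rise in false non-inferiority from 2.5% to between 4.0% and 28.8%, rest on assumed component rates, assumed detection loss and an SE back-calculated from the 4%. A reader might set the bias against 4% as if that were the non-inferiority margin. The sample size section gives it as a detectable difference from a superiority program, so a percentage of margin cannot be claimed.

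The documents do not support the stronger conclusion that the trial as a whole will tend to declare non-inferiority falsely, because other components may move the opposite way. They do show that a favourable composite result could not be taken at face value without separating these components.

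**What to change.** Before outcome data are examined:

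1. State which Table 3 variables form the primary obstetric composite and which are other variables.
2. Prespecify a supporting non-inferiority analysis on components whose recording does not depend on the number of visits, for example birth before 34+0, eclampsia, instrumental delivery, caesarean section and maternal death. It should not be co-primary: it leaves out preeclampsia, would rest on fewer events, and may be dominated by mode of delivery.
3. Report pregnancy-induced hypertension, preeclampsia and gestational diabetes separately by programme and label them schedule-dependent. Split hypertension and preeclampsia by whether first recorded before or at the delivery admission; a shift toward the admission under MAC would be direct evidence of later detection.
4. State that a lower MAC rate of these diagnoses will not be interpreted as benefit.

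The cost is some wording and one further analysis of register and record data the study already plans to extract. The supporting analysis will have fewer events and a wider interval. No change to care or to the visit schedule is involved.
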